# Impact of a medico-pharmaceutical follow-up and an optimized communication between hospital and community on the readmission to the emergency department for an adverse drug event: URGEIM, study protocol for a randomized controlled trial

**DOI:** 10.1186/s13063-021-05501-4

**Published:** 2021-08-06

**Keywords:** Emergency department, Pharmacist, Adverse drug event

## Abstract

**Background:**

Adverse drug events (ADE) represent one of the main causes of admission to emergency department (ED). Their detection, documentation, and reporting are essential to avoid readmission.

We hypothesize that a pharmacist-initiated multidisciplinary transition of care program combining ED pharmacist contribution and medications’ data transfer between inpatient and outpatient caregivers will reduce emergency visits related to ADE

**Method/design:**

This is a prospective, open-label, randomized controlled trial. The primary aim of the study is 6-month ED readmission related to the same ADE. Three hundred forty-six adult patients with an ADE detected by a binomial pharmacist-physician will be recruited from the ED of an University Hospital and will be randomized in two groups: [1] experimental group (multidisciplinary transition of care program and medications’ data transfer between inpatient and outpatient caregivers) and [2] control group (usual care). Patients will be followed up over a period of 6 months. Endpoints will be carried out blindly of the randomization arm. The primary endpoint is the rate of patients who had at least one readmission in the ED for the same reason at 6 months (data collected during a phone call with the patient and the general practitioner). Trials registered NCT03725046.

**Discussion:**

The trial results will have implications for the role of the clinical pharmacist in an emergency department. If successful, the intervention could be considered for implementation across other hospitals.

**Trial registration:**

ClinicalTrials.govNCT03725046. Registered on 30 October 2018

## Background

The hospital discharge process introduces care coordination challenges. A lot of patients, suffering from acute or chronic diseases, are evaluated to emergency departments for medical evaluation and subsequently discharged. On the border of hospital and community areas, emergency department (ED) realize a lot of medical consultations with a representative risk of communication failure with primary care providers. So many times, informative data failed to be transmitted to the general practitioners and are generally never transmitted to the community pharmacist.

Adverse drug events (ADE) represent one of the main causes of unplanned hospital admissions (up to 25%) and hospital deaths [1, 2]. ADE are defined as any patient damage, related to medication management and resulting from appropriate care, unsuitable care, or a lack of care. They are responsible for unfavorable clinical evolution and represent a major economic and healthcare problem [3, 4]. ADE require specific medication management to prevent any ADE recurrence and hospitalization.

Clinical pharmacist can improve transition of care (TOC), first by detecting ADE responsible of emergency visit and medication involved, then by making specific alert of primary care physicians improving medication management.

Many studies indicate that errors in TOC are common included detection and management of ADE [5–8]. Several strategies must be developed for limiting ADE recurrence, healthcare utilization, unplanned readmission, hospitalization, and/or death of the patients. Strategy to improve communication between healthcare providers is fundamental. Furthermore, pharmacists’ interventions (medication history end reconciliations, direct communication between providers and pharmacists, telephone follow-up with patients after discharge…) can limit ADE occurrence [1, 9–11].

Since November 2011, a pharmacy team is effectively integrated in ED of our hospital to help ED team about medication of inpatients: medication histories, ADE detection, and ADE management. We hypothesize that a pharmacist-initiated multidisciplinary TOC program combining ED pharmacist contribution and medications’ data transfer between inpatient and outpatient caregivers will reduce emergency visits related to ADE.

## Methods/design

### Aims of the study

The primary aim of the study is 6-month ED readmission related to the same ADE.

The secondary objectives are to evaluate the impact of this program at 6 months after admission for an ADE on:
All-cause ED readmission,ADE and all-cause hospitalization,ADE and all-cause mortality,ADE and all-cause healthcare utilization (primary care and specialist post discharge appointments)Medication modification related to the ADE

We will also evaluate in the “Intervention group”: the impact the program at 6 months on:
Satisfaction of community pharmacists and physiciansED pharmaceutical workload required to implement this discharge program.

### Study design

This is a prospective, monocentric, open-label, parallel group, randomized controlled trial. Patients with ADE are recruited from the ED of the University Hospital of Montpellier, France. Eligible participants are randomized to TOC program or usual care group. There is a 6 months follow-up, and the evaluation of the study outcomes is carried out blindly of the randomization arm. The study flow chart is presented in Fig. 1.

**Fig. 1 Fig1:**
[figure not shown]
Study flow chart

### Eligibility criteria

The participants, identified through ED, are aged from 18 and have an ADE (1/adverse drug reaction (ADR) without misuse, 2/ADR related to misuse and 3/nonadherence with unfavorable clinical repercussions). Moreover, pharmaceutical consultation with the patient or their relatives must be achievable and informed consent must be signed prior to inclusion in the study. Non-inclusion criteria are as follows: inability to carry out the patient’s drug history, ADE linked to medical care in the ED or voluntary drug intoxication, and pregnancy. Drop outs during the study include consent withdrawal, continuation of the study prejudicial to the patient according to the investigator, loss to follow-up, death occurring before hospital discharge, and patient hospitalized during more than 2 months after the admission to the ED.

### Randomization

Participants meeting the inclusion criteria are randomized by the ED pharmacist using a centralized computer generated randomization available on the e-CRF. Minimization randomization is used. Randomization (1:1) is stratified on the following criteria: type of ADE (linked to medication vs noncompliance), severity of the ADE (discharge from ED vs hospitalization), and age (± 70 years old).

### Recruitment and intervention

#### Detection of ADE

In the ED of the University Hospital of Montpellier, pharmaceutical management is currently offered upon arrival. Thus, in addition to the usual medical consultation, a pharmaceutical consultation is done from 8:30 a.m. to 6 p.m., from Monday to Friday (standard of care in our center). During this pharmaceutical consultation, the pharmacist carries out the best possible medication history (BPMH). The BPMH was defined as the most comprehensive list of all medications taken by the patient, including prescription drugs and self-medications, and was based on at least three sources of information (patient or family interview; drug prescriptions, if available; phone calls to community pharmacies, general practitioner and/or nurses; medical record). The interview is conducted following the recommendations of the World Health Organization [12]. ADE are detected based on the French method of pharmacovigilance imputation [13].

ADE are defined as any patient damage, related to medication management and resulting from appropriate care, unsuitable care, or a lack of care [4]. This definition included injuries (signs, symptoms or laboratory abnormalities) resulting from ADR or nonadherence with bad issue. Voluntary medication poisoning was excluded from the ADE definition. Event’s severity was classified into two categories: ED discharge or hospitalization.

Before participating in the study, physicians and pharmacists received training in detecting ADE. This training is provided by a multidisciplinary expert committee including one pharmacovigilant physician, one emergency physician, and one pharmacist. This group of experts has been collaborating since 2011 on ADE detection. In case of doubt about the ADE detection, the expert committee can be consulted.

When ADE is detected, the ED pharmacist describes the study to the patient. Subjects willing to participate sign an informed consent form before the baseline evaluation, data collection and randomization.

#### Experimental intervention

ED pharmacist makes a 72-h post discharge alert using telephone call. This follow-up call improves direct communication between the general practitioner and the community pharmacist of the patient and is an opportunity to discuss ADE management. A specific ADE alert leading to ED visit is sent to the general practitioner in addition to the letter of discharge (usual care). The specific ADE alert is written and validated by the ED physician and ED pharmacist, including ADE type and suspected medication as well as any recommendation (therapeutic modification, referral to specialized consultations, names and contact information to easily reach the physician and the pharmacist involved in the treatment charge in the ED) (see Fig. 2).

**Fig. 2 Fig2:**
[figure not shown]
Schedule of enrolment, intervention, and assessments

#### Control intervention

A letter of discharge specifying the reason for emergency admission is sent to the general practitioner (standard of care).

### Outcomes

Outcomes will be collected during a phone call by a pharmacist blindly of the randomization arm, with the patient at 3 and 6 months and with general practitioner at 6 months. When available, outcomes will be confronted with data from the patient’s electronic medical file. The phone call at 3 months avoids the risk of loss of contact with patients.

The primary endpoint is the rate of patients with at least one same ADE leading to ED readmission at 6 months.

Secondary endpoints evaluated at 6 months are:
Rate of patients who had at least one all-cause ED readmissionRate of patients who had at least one ADE hospitalization and all-cause hospitalizationRate of potentially preventable hospitalizations based on the definition of the American agency AHRQ adapted to French data [14]Rate of ADE and all-cause deathRate of ADE and all-cause medical consultations (general practitioner and specialists)Rate of medication modification.

In the intervention group, we will also collect the satisfaction of healthcare referrals (general practitioners and pharmacist) evaluated with a Likert-like scale and pharmaceutical time required to implement the intervention.

We will also collect patients’ characteristics (sociodemographic data, comorbidities), medications (name, dosage, compliance, modification during the last 15 days), characteristics of ADE (type, severity), and, for the interventional group, the type and number of pharmacist recommendations.

An electronic case report form (e-CRF) is developed by the Clinical Research and Epidemiology Unit from the software Ennov Clinical® to collect and to control data quality at entry and during the trial. Data collected in the e-CRF are pseudo-anonymized (subject identification code and subject initials).

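### The primary endpoint can be ascertained differently by arm, because general practitioners who report on 'same ADE' readmissions are given ADE-specific information in the experimental arm only

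*Protocol article*

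**What the plan says.** All references are to the protocol article.

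- **Endpoint (Outcomes).** "The primary endpoint is the rate of patients with at least one same ADE leading to ED readmission at 6 months". The abstract words it as a readmission "for the same reason at 6 months (data collected during a phone call with the patient and the general practitioner").
- **Source (Outcomes).** "Outcomes will be collected during a phone call by a pharmacist blindly of the randomization arm, with the patient at 3 and 6 months"; the same sentence adds the GP at 6 months. The next sentence gives a cross-check: "When available, outcomes will be confronted with data from the patient’s electronic medical file".
- **Blinding (Study design).** The trial is open-label. Outcome evaluation is stated to be blind to arm, and the abstract says the same of the endpoints.
- **Experimental arm (Experimental intervention).** "A specific ADE alert leading to ED visit is sent to the general practitioner in addition to the letter of discharge (usual care"). The alert covers the ADE type, the suspected drug and any recommendation. There is also a telephone alert 72 hours after discharge, which serves to discuss ADE management with the GP and the community pharmacist.
- **Control arm (Control intervention).** "A letter of discharge specifying the reason for emergency admission is sent to the general practitioner (standard of care").
- **Entry ADE (Detection of ADE).** "ADE are detected based on the French method of pharmacovigilance imputation [13"], with an expert committee available in case of doubt.

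**The concern.** The endpoint is not a plain count of ED visits. Someone has to decide that a later visit was caused by the same ADE as the first. A GP can help with that only by knowing which ADE and which drug lay behind the index visit, and supplying that knowledge is what the intervention does, in one arm. The Background section itself says that information often fails to reach GPs. The trial therefore acts on a knowledge gap and then uses the people on either side of it as a source for the primary outcome.

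Two opposite distortions are possible. Better-informed experimental GPs may recognise more same-ADE readmissions, which would shrink a real benefit or suggest harm. Informants who know the programme was delivered may report less, which would exaggerate benefit. A blinded caller prevents neither. The secondary endpoints attributed to an ADE (hospitalisation, death, consultations) share the weakness.

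**Working it through.** **1. The plan's own figure.** Inputs from Sample size: 14% against 5%, two-sided alpha 0.05, power 80%, 314 patients, 10% dropout, 173 per group. With the arcsine formula,

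h = 2·asin(√0.14) − 2·asin(√0.05) = 0.316

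n = 2·[(1.960 + 0.842)/h]² = 157.2 per arm, or 314 in total.

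Then 157 × 1.10 = 172.7, which gives 173. The stated size reproduces and is not in dispute here.

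**2. Number analysed.** 173 × 0.90 = 155.7, taken as 156 per arm.

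**3. Model for differential recognition.** Observed rate = true rate × probability that a same-ADE readmission is recognised as such. No false attributions are assumed. The documents give no recognition rates; 90, 80 and 70% are assumptions chosen to show a range.

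**4. Test.** Pearson chi-square without continuity correction. With x and y events in the two arms and p̄ = (x + y)/(2n),

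z = (x/n − y/n) / √[2p̄(1 − p̄)/n]

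The rejection probability is the exact sum of Bin(x; 156, p_C) × Bin(y; 156, p_E) over all pairs with |z| > 1.96.

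**5. True rates 14% and 5%, experimental arm fully recognised.**

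| Control recognition | Observed control rate | Observed difference | Power |
|---|---|---|---|
| 100% | 14.0% | 9.0 points | 79% |
| 90% | 0.90 × 14 = 12.6% | 7.6 points | 67% |
| 80% | 0.80 × 14 = 11.2% | 6.2 points | 52% |
| 70% | 0.70 × 14 = 9.8% | 4.8 points | 36% |

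In counts, the control arm expects 156 × 0.14 = 21.8 patients with an event. Missing 20% of them means 4.4 patients, so a handful of labels decides the result.

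**6. No true effect, 14% in both arms, one arm under-recognised.**

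| Recognition in that arm | Two-sided rejection | In favour of the under-recognised arm |
|---|---|---|
| 100% | 4.9% | 2.5% |
| 80% | 11.5% | 11.1% |
| 70% | 20.9% | 20.8% |

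The table is symmetric. If controls are under-recognised, the false result is harm from the programme; if experimental events are under-reported, it is false benefit.

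**7. Cross-check.** The normal approximation at 157 per arm gives power of 78, 66, 52 and 37% for step 5, and 11.6 and 20.9% for step 6.

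**The case against.** The best defence is that one procedure applies to both arms: same calls, same timing, same blinded caller, same file check. Blinded evaluation is stated as well as blinded collection. Nowhere does the article say that the patient or GP decides whether a visit was the same ADE; they supply information to a blinded pharmacist. The e-CRF holds the index ADE and the medications for every patient, so a comparison with the index event is possible in either arm. Much of this stands. A reader might infer that the endpoint *is* ascertained differently by arm; the documents show only that it can be.

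A second tempting reading is that patients too are made more knowledgeable in one arm. The documents do not support it. The alert and call are directed to the GP and community pharmacist, and in both arms the study is described to the patient after an ADE has been detected. The documented difference is limited to GP reports. Control GPs are not uninformed either, since their letter gives the reason for the visit; whether it names the ADE or the drug is not stated.

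A third reading is that the imputation method used at entry has been dropped for the outcome. The article is silent on this. It condenses a full protocol that is not shown, so silence is not evidence of a decision.

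The figures also have limits. The recognition rates are assumed, and the power table runs in one direction only. The model treats a missed GP label as a missed event, although patient calls and the file are parallel sources. All-cause ED readmission, already a secondary endpoint, needs no attribution and offers a built-in check.

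What survives is that blinding the person who asks and the person who evaluates does not blind the person who answers, and that the record check is conditional.

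**Conclusion.** The concern holds as a risk, not as a demonstrated bias. It rests on four points in the text: an open-label trial, a primary endpoint that needs causal attribution, telephone collection from patients and GPs, and ADE-specific information sent to experimental-arm GPs alone. The net direction is undetermined. The size is illustrative and depends on assumed recognition rates, complete recognition in the other arm, no false attributions and 156 per arm. Under those assumptions, a 10 to 30 point shortfall in control recognition takes power from 79% down to between 67% and 36%. With no true effect, 80 or 70% recognition in one arm takes the two-sided error to about 11.5 or 21%. The change should be made because it is cheap and uses people and methods already in the trial.

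**What to change.** In Outcomes, separate finding ED visits from attributing them:

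- Use the calls in both arms to locate ED visits (date and place), and search this hospital's ED file for all randomised patients.
- Have the already planned blinded pharmacist classify every ED readmission as same ADE, other ADE or not ADE from the ED record, with arm and alert removed. Use the imputation method applied at inclusion and refer doubtful cases to the existing expert committee.
- Let the record take precedence over informant statements. Use informant reports only where no record can be obtained, and report how often that happens by arm.
- Read the primary result beside all-cause ED readmission.

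The sample size and the intervention do not change. The cost is a wording change and record-review time, partly retrospective because 288 patients had been included by August 2020 (Trial status). Some bias can remain where records from other hospitals are missing, which is why the count by arm should be shown.

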### Harms

The investigator is responsible for collecting all the adverse events throughout the study. They will be assessed at each visit and reported in the e-CRF. Harms reporting will be carried out in compliance with the French regulations in force throughout the study. There are no anticipated harms. The sponsor of the study takes out insurance for the entire duration of the study guaranteeing its own civil liability as well as that of any party involved in the study.

### Monitoring and audit

On-site or remote monitoring visits will be realized by the monitors designated by the sponsor to check compliance with the protocol, the completeness, accuracy and consistency of the data, and adherence to Good Clinical Practice (GCP). During the trial, an audit could be organized by the sponsor or competent authority. The audit can be applied at all stages of research, from protocol development to publication of results. This study does not have a data monitoring committee due to low risk interventions.

### Sample size

The study by Zhang M et al. showed 17% of hospital ADE readmission. This rate is based on data from medical coding which probably underestimate this rate [15]. A descriptive pre-study carried out in the study center to assess the impact of specific ADE alert to community health professionals in case of ADE showed a rate of emergency readmissions of 13.7% without transmission of the medico-pharmaceutical report and a rate of 5.1% with transmission. Assuming a 14% readmission rate in the control group and a rate of 5% in the TOC group, a sample size of 314 subjects is required with two-sided alpha = 0.05 and a power of 80%. To take into account a 10% dropout rate, 173 subjects per group will be included.

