### Statistics and data analysis

The statistical analysis will be performed by the Clinical Research and Epidemiology Unit at the Montpellier University Hospital using SAS software (SAS Institute, Cary, NC, USA). The level of significance is set at *p* < 0.05 (bilateral).

Statistical analysis will be performed on the intention to treat (ITT) population. The decision to perform analyses on other population sets for sensitivity analysis will be taken by the study methodologist if necessary.

The number of screened, included, and randomized patients in each group will be summarized in a flow chart. Excluded and lost to follow-up patients will be reported.

Patients’ characteristics in the total population and in each group will first be analyzed. Quantitative variables will be expressed by mean, standard deviation, median, range, and quartiles. Qualitative and categorical data will be summarized by frequencies and percentages. Characteristics will be compared between the two groups using Student’s *t* test or Mann-Whiney *U* test for continuous variables and chi-square or Fisher exact test for categorical variables.

The distribution of the main outcome will be compared between the two groups with chi-square or Fisher exact test. Logistic regression models will also be implemented to analyze the effect of the group on the main outcome by adjusting on variables of interest. Univariate models will first be executed, and the variables with a *p* value lower than 0.15 will be considered for a multivariable model. Then, the variables with a *p* value lower than 0.05 in the multivariable model after a stepwise selection of variables will be considered statistically significant.

Categorical secondary outcomes will be analyzed using the same methodology as the main outcome, with chi-square or Fisher exact test and logistic regression models. Quantitative secondary outcomes will be compared between the two groups using Mann-Whiney *U* test, along with multivariable linear regressions with covariates of interest.

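### The 10% dropout allowance is multiplied on rather than divided out, so 346 patients leave about 311 analysed, 3 below the 314 stated as required

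*Protocol article*

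**What the plan says.** The Sample size section of the protocol article sets the planning rates: "Assuming a 14% readmission rate in the control group and a rate of 5% in the TOC group". From these it concludes that "a sample size of 314 subjects is required with two-sided alpha = 0.05 and a power of 80" per cent. It then adds the allowance for loss: "To take into account a 10% dropout rate, 173 subjects per group will be included". The abstract gives the same total: "Three hundred forty-six adult patients with an ADE detected by a binomial pharmacist-physician will be recruited". The section names no sample-size formula or software.

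Under Randomization, allocation is 1:1. Under Statistics and data analysis, the primary comparison is described thus: "The distribution of the main outcome will be compared between the two groups with chi-square or Fisher exact test". The same section says: "Statistical analysis will be performed on the intention to treat (ITT) population".

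**The concern.** The section gives two figures that should agree. One is the number needed for the stated power (314). The other is the number to include so that this many remain after 10% are lost (346). Taking 10% off 346 does not give back 314.

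A reader who relies on the section would take it that the trial keeps its stated power under the dropout it plans for. At stake is whether that holds, and by how much it fails if it does not.

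**Working it through.** **Inputs.** Control rate 14%, intervention rate 5%, two-sided alpha 0.05, power 80%, 314 required, 10% dropout and 173 per group are all from Sample size. The 1:1 allocation is from Randomization. The total of 346 is from the abstract and equals 2 x 173.

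**Step 1: reproduce the 314.** The arcsine formula is n per arm = 2(z_alpha/2 + z_beta)^2 / h^2, with h = 2 arcsin(sqrt(p1)) - 2 arcsin(sqrt(p2)).

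- h = 0.7670 - 0.4510 = 0.3160
- (1.960 + 0.8416)^2 = 7.849
- n = 2 x 7.849 / 0.3160^2 = 157.2 per arm, or 314.5 in total

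So 314 (157 per arm) reproduces, apart from rounding down by a fraction of a patient.

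**Step 2: check that 314 does what is claimed.** I enumerated the two binomial distributions and summed the probability of every table that an uncorrected chi-square test rejects at 0.05.

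| Per arm | Total | Exact power, 14% vs 5% |
|---|---|---|
| 155 | 310 | 79.1% |
| 156 | 312 | 79.4% |
| 157 | 314 | 79.6% |
| 158 | 316 | 79.9% |
| 159 | 318 | 80.2% |
| 166 | 332 | 82.1% |
| 173 | 346 | 83.8% |

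At 157 per arm the power is 79.6%, which is 80% to the precision stated.

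**Step 3: reproduce the 346.** Multiplying gives 314 x 1.10 = 345.4, rounded up to 346, or 173 per arm. This matches the plan.

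**Step 4: apply the planned dropout to the planned number.** 346 x (1 - 0.10) = 311.4, so about 311 patients are analysed. 314 - 311 = 3 short. Put differently, 346 protects 314 only up to a loss of (346 - 314) / 346 = 9.2%, not 10%.

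**Step 5: the allowance done correctly.** n / (1 - d) = 314 / 0.90 = 348.9, so 349, or 350 with equal arms (157 / 0.90 = 174.4, so 175 per arm). The planned 346 is 3 or 4 patients lower.

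**Step 6: the cost in power.** About 311 analysed means 155 to 156 per arm, with exact power of 79.1% to 79.4%. Against 79.6% at 157 per arm, the loss is:

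- at 156 per arm: 79.65 - 79.36 = 0.3 points
- at 155 per arm: 79.65 - 79.07 = 0.6 points

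**The case against.** **The slip changes nothing in practice.** It amounts to 3 or 4 patients and about half a point of power. The primary analysis is also by intention to treat, so if an outcome were obtained for all 346, exact power would be 83.8%. This objection stands on size, and it is why the point is minor. It does not remove the inconsistency. The section itself plans for 10% loss, and on that assumption 346 does not leave 314.

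Three stronger readings are tempting, and the documents support none of them.

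- **That 314 is too small because the chi-square test needs 332.** The pooled normal formula does give 165.4, so 166 per arm and 332 in total. It is one approximation among several, and here a conservative one: it puts power at 157 per arm at 77.9%, against an exact 79.6%. Exact power passes 80% at 159 per arm (318 in total). The article names no formula, which an article may leave to the full protocol, and a standard formula reproduces its figure.
- **That power is really about 74%, because Fisher's exact test is allowed.** Fisher's exact power at 157 per arm is 74.0%. But chi-square or Fisher is conventional wording, with Fisher kept for small expected counts. At the planning rates about 22 and 8 events are expected (157 x 0.14 and 157 x 0.05), so the smallest expected cell is about 15. The chi-square test would apply.
- **That rounding 13.7% and 5.1% to 14% and 5% is an error.** The section states the pre-study rates and then openly assumes the rounded ones. The pooled formula would ask for 180 per arm at the unrounded rates. That shows sensitivity to a declared assumption and is not a miscalculation.

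**Conclusion.** The point holds for the dropout allowance only. The plan multiplied by 1.10 where it should have divided by 0.90, so at its own dropout rate it keeps about 311 patients against a stated requirement of 314. This does not depend on how the 314 was obtained.

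The effect is well under one percentage point: about 79% power instead of 79.6%. These power figures assume true rates of 14% and 5%, near-equal arms, an uncorrected chi-square test at two-sided 0.05, and 10% of patients without an outcome and left out of the comparison. The trial is not materially underpowered on its own assumptions.

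**What to change.** Keep 346 and correct the statement. For example: 346 patients (173 per group) will be randomised; with 10% dropout about 311 will be analysed, which gives about 79% power to detect 14% versus 5% (exact, uncorrected chi-square, two-sided alpha 0.05); if all 346 have an outcome, power is about 84%. Wherever the inflation is described, give it as n / (1 - 0.10), under which 314 would become 349, or 350 with equal arms.

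The change costs wording only and needs no further patients. Its one drawback is a stated power slightly less favourable than 80%.
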